## Abstract

**Background:**

Irritable bowel syndrome (IBS), a functional bowel disorder with symptoms of abdominal pain and disturbed defecation experienced by 10% of U.S. adults, results in significant disability, impaired quality of life, and health-care burden. Conventional medical care focusing on pharmacological approaches, diet, and lifestyle management has been partially effective in controlling symptoms. Behavioral treatments, such as cognitive-behavioral therapy and hypnosis, are promising. This paper describes an on-going feasibility study to assess the efficacy of mindfulness training, a behavioral treatment involving directing and sustaining attention to present-moment experience, for the treatment of IBS.

**Methods/Design:**

The study design involves randomization of adult women with IBS according to Rome II criteria, to either an eight-week mindfulness training group (based on a Mindfulness-based Stress Reduction [MBSR] format) or a previously validated IBS social-support group as an attention-control condition. The primary hypothesis is that, compared to Support Group participants, those in the Mindfulness Program will demonstrate significant improvement in IBS symptoms as measured by the IBS Symptom Severity Scale [1].

**Discussion:**

214 individuals have been screened for eligibility, of whom 148 were eligible for the study. Of those, 87 were enrolled, with 21 withdrawing after having given consent. 66 have completed or are in the process of completing the interventions. It is feasible to undertake a rigorous randomized clinical trial of mindfulness training for people with IBS, using a standardized MBSR protocol adapted for those experiencing IBS, compared to a control social-support group previously utilized in IBS studies.

**Trial Registration:**

Clinical Trials.gov Identifier: NCT00680693

## Background

Irritable bowel syndrome (IBS) is a functional bowel disorder characterized by symptoms of abdominal pain or discomfort associated with disturbed defecation [2], experienced by about 10% of the U.S. adult population (14% women, 8% men), and resulting in disability, impaired quality of life, and health-care burden [3-5]. Conventional medical care for IBS has focused on diet and lifestyle management (e.g. exercise and stress reduction), behavioral treatments, and a range of pharmacological approaches, particularly antispasmodics [6]. Pharmacological therapies, which often bear significant costs and side effects, may relieve symptoms temporarily but seldom correct underlying causes. Behavioral treatments, such as cognitive-behavioral therapy and hypnosis, have shown positive results, reflecting the importance of a biopsychosocial perspective.

Mindfulness meditation is a unique behavioral technique which involves the intentional self-regulation of attention by learning to attend to present-moment experience and letting go of cognitive fixation on thoughts of past and future, thus inducing a non-evaluative metacognitive state. Mindfulness practice has been shown to reduce symptoms of stress and pain and ameliorate the symptoms of fibromyalgia and depression [7-11]. There is little research, and no well controlled clinical trials, on its efficacy specifically for IBS. One small, uncontrolled pilot study at UNC found decreased symptom severity in patients with IBS following an eight-week mindfulness-training program [12].

A study of mindfulness for treatment of IBS is warranted for the following reasons: 1) mindfulness training has been shown to be associated with significant symptom reduction in disorders in which both pain and stress are prominent; 2) the techniques of mindfulness can be taught effectively in groups; 3) mindfulness programs are taught as wellness programs, with participants typically reporting positive changes in life-style in addition to improved stress and pain management; 4) as wellness programs, mindfulness can be taught safely and effectively by instructors who may be unlicensed in other disciplines but well-trained in mindfulness; 5) participants report high levels of satisfaction and drop-out rates are low.

Mindfulness meditation may be uniquely suited to treat the underlying psychological symptoms associated with IBS: these include an increased sensitivity to pain from intestinal distention [13] that is correlated with anxiety about the significance of these sensations [14] and selective attention to gastrointestinal sensations [15]. Indeed, recent cognitive neuroscience investigations have found that mindfulness meditation induces alterations in the activation of neural circuits implicated in neurovisceral awareness, interoception (sensitivity to internal stimuli), and self-regulation [16,17]. Additionally, mindfulness has been shown to improve ability to control attentional processes [18-21]. Given these findings, it seems plausible that mindfulness may exert a salutary effect on irritable bowel symptomatology and perhaps even the underlying mechanisms of the syndrome.

In this paper, we describe an ongoing feasibility study to assess the efficacy of a program of mindfulness-based stress and pain management (Mindfulness Program) for treatment of IBS-related symptoms in women. The study includes baseline assessments in patients with documented IBS with subsequent randomization to one of two treatment arms: 1) Mindfulness Program (the intervention group); and 2) an IBS Support Group (the control group) previously validated as an effective placebo-control condition in a randomized controlled trial of cognitive behavior therapy for the treatment of IBS [22]. Outcomes are evaluated at the end of treatment and at 3, 6, and 12 months follow-up.

The study's primary aim is to determine the feasibility of developing a clinical trial comparing effectiveness of a Mindfulness Program with an IBS Support Group in reducing the severity of symptoms in women with IBS. The primary hypothesis is that, compared to those in the Support Group, those in the Mindfulness Program will demonstrate significant improvement in IBS symptoms, as measured by the IBS Symptom Severity Scale [1].

Aim two is to identify appropriate secondary outcomes in the Mindfulness Program and IBS Support Groups, including psychological symptoms, coping strategies, and quality of life. We hypothesize that, compared with those in the Support Group, those in the Mindfulness Program will experience significant reductions in anxiety, depression, anger, and maladaptive coping strategies, as well as improvements in quality of life and effective occupational functioning. Analysis of these variables will lead to better estimates of effect sizes and powering of future studies, and will guide the selection of outcome measures and the design and analyses for those studies.

A third aim is to compare two currently available process measures of mindfulness – the Five Facet Mindfulness Questionnaire (FFMQ) [18-21] and the Toronto Mindfulness Scale (TMS) [23], specifically testing: a) how well the FFMQ vs. the TMS are able to detect any differences in treatment groups; and b) whether either of these scales can discriminate those assigned to the Mindfulness Program who are ranked as more successful at learning and practicing mindfulness from those who are less successful.

## Methods/Design

Figure 1 illustrates the overall design and subject flow through the study. Study procedures and consent forms were reviewed and approved by the Institutional Review Board of The University of North Carolina at Chapel Hill (UNC).

**Figure 1 F1:**
[figure not shown]
**Overall Design and Subject Flow**.

### Hypotheses

The primary hypothesis is that, compared to those in the Support Group, those in the Mindfulness Program will demonstrate significant improvement in IBS symptoms, as measured by the IBS Symptom Severity Scale [1]. Secondary hypotheses are that, compared with those in the Support Group, those in the Mindfulness Program will experience significant reductions in anxiety, depression, anger, and maladaptive coping strategies, as well as improvements in quality of life and effective occupational functioning.

### Eligibility

Included in this trial are women at least 18 years old who have a medical diagnosis of IBS and who also meet the Rome II criteria for IBS [24]. Subjects must be able to understand English and be willing and able to document regularly their IBS symptoms and medication use as well as complete the assessment instruments. Subjects must be willing to attend 8 weekly 2-hour Mindfulness Program or Support Group sessions plus a half-day Saturday session. All subjects are informed that they should continue to receive usual care from their primary care or specialist physicians and that no specific recommendations for changes in medications for IBS or other medical issues will be made by the research team.

Excluded are subjects with the following conditions: 1) diagnosis of mental illness with psychotic features; 2) a history of an inpatient admission for psychiatric disorder within the past two years; 3) a history or current symptoms of inflammatory bowel disease or gastrointestinal malignancy; 3) active liver or pancreatic disease; 4) uncontrolled lactose intolerance; 5) celiac disease; 6) a history of abdominal trauma or surgery involving gastrointestinal resection; or 7) pregnancy or intention to become pregnant during the study.

### Recruitment

Patients under the care of the UNC Health Care System or local community physicians are recruited through several sources: 1) advertisements on the website of the UNC Center for Functional GI and Motility Disorders ; 2) newspaper advertisements; 3) an existing IBS patient registry; 4) posters and brochures; and 5) mass e-mailings to UNC list-serves. Additionally, physicians are asked to inform patients with IBS about the study, describing it as a psychological support intervention to be carried out in addition to their usual conventional therapy for IBS. Study participants are remunerated for completing the assessments and as well as for completing the assigned intervention (defined as attendance at a minimum of six of the nine sessions).

### Screening, consent, and enrollment

Prospective subjects are screened by telephone by the study coordinator. If an individual is eligible for the study and wishes to participate, the study coordinator schedules a meeting at a mutually convenient time and location to explain the study, obtain informed consent, and complete initial assessments. A psychosocial assessment and gastrointestinal medical questionnaire is completed at this visit or shortly thereafter. Subjects are told that they may have to wait a short time for classes to begin while additional subjects are being recruited. Classes are scheduled to begin when a minimum of 6 subjects have been randomized to each of the two groups.

### Randomization

Upon completion of the baseline interview and questionnaires, eligible women are randomized by computer to the Mindfulness Program or IBS Support Group. This process eliminates experimenter bias in group assignment. The computer program uses a random number generator and is programmed to insure equal numbers of subjects in each arm of the study within a variable block size of 4–8 subjects. The computer program generates a treatment assignment and a study ID number associated with each eligible subject's name and birth date, and documents these in an uneditable form with a date stamp.

### Masking

The nature of the interventions does not allow masking of treating physicians, subjects or instructors. To minimize differences in subject expectancy, the experimental interventions are described to subjects only as two psychological interventions – a set of meditation procedures and a support group – both of which have been reported in previous studies to benefit patients with IBS. The intent is to prevent subjects from knowing which intervention the investigators believe is most likely to improve symptoms. To verify that patients assigned to the Support Group have the same expectation of benefit as patients assigned to the Mindfulness Program, all patients complete a Credibility Scale [25] after the first treatment session. This scale is presented to the subjects as an "early evaluation" scale.

Follow-up questionnaires are printed and mailed to subjects for completion. To maintain masking of staff involved in data input and analysis and to prevent bias, returned questionnaires bear only a research number.

### The Intervention Group – Mindfulness for Irritable Bowel Syndrome

The mindfulness-based stress and pain management program (Mindfulness Program) was based on the Mindfulness-Based Stress Reduction (MBSR) program developed by Jon Kabat-Zinn and Saki Santorelli at the University of Massachusetts. MBSR is a flexible program, adaptable to a variety of patients with wide-ranging symptoms [26]. The modification introduced was to emphasize symptoms and perceptions concerning IBS when teaching about mindfulness, as well as in group discussion. For example, it is suggested to participants that they might notice any sensations in the abdominal area and distinguish those sensations from thoughts *about *sensations. In so doing, the mindfulness intervention targets maladaptive cognitive coping styles such as catastrophizing, which have been shown in the literature to exacerbate irritable bowel symptoms [27,28].

In keeping with the MBSR program, the Mindfulness Program consists of one 2-hour session each week for 8 consecutive weeks plus a Saturday retreat near the end of the intervention. For the Saturday retreat setting of the Day of Mindfulness, we shortened the length of the day from six to four hours to match the length of time of the Support Group's Saturday session.

#### Class 1

The course begins with personal introductions to create group cohesion, an overview of the coming eight weeks, and a discussion of attitudes that support mindfulness. Participants are led through an experiential exercise that focuses on the immediacy of physical sensations and differentiates sensations from thoughts *about *sensations; they are encouraged to take this practice home as mindful eating. They are introduced to diaphragmatic breathing. Participants are then led through a lengthy scan of body sensations to facilitate non-judgmental awareness; this exercise is also assigned as part of routine home practice, along with weekly readings of relevant chapters in *"Full Catastrophe Living" *and "*IBS for Dummies."*

#### Class 2

Participants are guided through the body scan at the beginning of class. They are then encouraged to share and discuss their experiences during the preceding week, particularly with regard to home practice. Participants are introduced to sitting meditation with awareness of breathing as the primary object of attention, partially for the purpose of developing concentration. This form of meditation is added to the daily home practice, along with continuation of the body scan and new readings. The role of subjective interpretation is also presented as a way of beginning to understand personal responsibility for one's thoughts and actions. Home practice this week also includes awareness of pleasant events and of a routine daily activity.

#### Class 3

Gentle mindful yoga movements are introduced as a way of alleviating physical symptoms of stress and bringing awareness to subtle movements of the body. The discussions include the power of being in the present moment and the objective observation of thoughts as *merely thoughts*, rather than as facts or events. Home practice now includes body scan, gentle yoga, sitting meditation with focus on breathing, awareness of unpleasant events, and awareness of a different routine activity.

#### Class 4

The practice of sitting meditation is expanded to emphasize the perception of body sensations *as simply sensations *(as opposed to interpretations and thoughts *about *sensations, e.g. catastrophizing). Walking meditation is also introduced. The psychophysiology of the stress response is presented. Recommended home practice at this point consists of alternating body scan, gentle yoga, walking meditation, sitting meditation (for a longer period of time), and bringing awareness to both stress reactions and to moments of going numb or shutting down.

#### Class 5

Acknowledging the halfway point in the course, participants discuss commitment to daily practice and their experiences of the effects of the program so far. Sitting meditation is expanded to include awareness of thoughts arising and passing away, followed by a discussion of the role of mindfulness in responding to stress in everyday life. The concept of emotional intelligence is introduced. For home practice, participants are encouraged to begin experimenting with combinations of practices previously introduced that fit their needs, including body scan, gentle yoga, walking meditation, and sitting meditation. Home practice also includes a difficult communications exercise and awareness of the distinction between everyday reacting (without choice) and responding (with choice).

#### Class 6

Sitting meditation continues to lengthen and deepen via guided practice sessions that include use of metaphors that explore qualities of mindfulness. The topic of working with emotions continues from the previous class, expanding the inner resources for emotional resilience. In addition to the home practices suggested previously, participants are asked to be aware of and label their emotions for the next week.

#### Half-day Retreat

Most of the time is spent in silence, with alternating periods of sitting meditation, walking meditation, gentle mindful yoga, a body scan, and an introduction to a guided loving-kindness meditation. A discussion period at the end allows participants to share their experiences, challenges, and insights.

#### Class 7

The practice of *choiceless awareness *is introduced to the sitting meditation. Choiceless awareness is a state in which one is fully aware of the moment, yet mindfulness is not focused on any physical or mental image or object. Topics of discussion include gaining confidence in the practice and results of mindfulness, awareness as related to food and eating, and experiences in everyday life following the half-day retreat. In addition to the home practices suggested previously, attention is drawn to awareness of how we nourish our bodies, and how that relates to emotional intelligence.

#### Class 8

Class begins with a body scan, followed by sitting meditation. The discussion focuses on a brief review of the course, acknowledging where the participants are at this point in their personal practices, and cultivating resources for continued practice.

Homework assigned each week throughout the course includes daily mindfulness practices and readings from two provided texts, "*Full Catastrophe Living*" [26] and "*IBS for Dummies*" [29]. Subjects are asked to keep a daily diary, including minutes of practice time and any IBS symptoms. Subjects may choose to record diary information either electronically (submitted daily) or on paper (submitted weekly at the meetings or mailed).

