Each session begins with an introduction of the specific IBS-related topic by the group leader. Subjects are encouraged to provide examples from their own life experiences to enhance each other's understanding of the topic. Although Support Group leaders facilitate discussion and answer questions, they do not give didactic information, behavioral prescriptions, or advice. Instead, the role of the group leader is to prompt participants with questions, facilitate discussion, and maintain an environment where disclosure is possible. To that end, leaders ask open ended questions, and promote discussion by using probes such as asking for clarification, requesting explanations, and encouraging cross-talk between group members. If subjects ask the group leader a direct question about how to manage their IBS symptoms, the group leader responds by redirecting the question to the group and urging participants to share their own coping strategies with one another.

Homework assigned each week throughout the course includes readings from the provided text, *"IBS for Dummies*" [29]. Subjects are asked to write a journal entry about the discussion topic for the coming week as it relates to their personal experience with IBS, as well as to keep a daily diary of IBS symptoms. Subjects may choose to record journal/diary information either electronically (submitted daily) or on paper (submitted weekly at the meetings or mailed).

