***Secondary Outcome measures***		

Symptom frequency	Daily Symptom Diary	Daily during the intervention and for 2 weeks post

IBS-related anxiety	Visceral Sensitivity Index	Pre, 2 wk, 3 mo, 6 mo, 12 mo post

Economic impact of IBS	The Work Productivity and Activity Impairment for IBS (WPAI: IBS)	Pre, 2 wk, 3 mo, 6 mo, 12 mo post

Co-Morbid Symptoms	Recent Physical Symptoms Questionnaire (RPSQ)	Pre, 2 wk, 3 mo, 6 mo, 12 mo post

General psychological distress	Brief Symptom Inventory (BSI)	Pre, 2 wk, 3 mo, 6 mo, 12 mo post

Anger and its expression	The State-trait Anger Expression Inventory (STAXI)	Pre, 2 wk, 3 mo, 6 mo, 12 mo post

Maladaptive coping methods	Coping Strategies Questionnaire (CSQ)	Pre, 2 wk, 3 mo, 6 mo, 12 mo post

Quality of life specific to IBS	IBS-QOL	Pre, 2 wk, 3 mo, 6 mo, 12 mo post

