#### Secondary outcome variables

##### Daily Gastrointestinal Symptom Diary

The symptom diary was adapted from Blanchard et al. [32] Subjects are asked to complete daily symptom ratings on the Internet, using a password-protected web page, or on a paper version of the same diary. On separate 0–4 scales, subjects rate how much of a problem they have had in the past day with abdominal pain and tenderness, constipation, diarrhea and bloating. They are also asked to record whether symptoms interfered with eating, drinking or their usual activities, and how many minutes they did homework related to the study. A space is provided for other comments.

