##### Quality Control (See Table 2)

**Table 2 T2:** Quality Control and Feasibility Measures

Component	Measure	Responsible party
Context	Log of comments about space, contacts with other interested parties outside of participants	Instructors Study coordinator

Dose delivered	Attendance log Enrollment diary	Instructors Study coordinator

Dose received	Participant log of adherence to homework assignments	Instructors

Fidelity	Video-taping of instructors delivering interventions	Research assistant, PI

Instructors record attendance, logistical problems and other study-related issues. The study coordinator keeps a similar log of logistical issues and contacts subjects not completing the intervention to evaluate factors leading to dropout. To evaluate subject engagement, subjects are prompted to keep a log of their homework practice in their daily diaries.

To evaluate intervention fidelity, we measure instructor adherence to protocol through videotaping the second and seventh Mindfulness Program and IBS Support Group sessions with an unmanned stationary video recorder. Video-taping is for purposes of identifying variations in instructor attitude, communication bias and systematic variations in behavior between treatment groups. It is also used to assess adherence to protocol as well as to screen for any group-dependent differences in content or style of communication between the instructor and participants.

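### The symptom diary shares a form with the homework log and may be handed in on paper at class, so unmasked leaders may see a secondary outcome

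*Protocol article*

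**What the plan says.** **Status of the diary.** Table 1 lists the Daily Symptom Diary among the secondary outcomes, collected "Daily during the intervention and for 2 weeks post". The analytic strategy section plans GEE models for the daily symptom records, on the same lines as for the IBSS.

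**Content.** The description of the Daily Gastrointestinal Symptom Diary has separate 0–4 ratings of pain, constipation, diarrhea and bloating. It also asks women to record "how many minutes they did homework related to the study". For the Mindfulness arm, the homework paragraph after Class 8 says: "Subjects are asked to keep a daily diary, including minutes of practice time and any IBS symptoms". Under Quality Control, "subjects are prompted to keep a log of their homework practice in their daily diaries".

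**Return, Mindfulness arm.** "Subjects may choose to record diary information either electronically (submitted daily) or on paper (submitted weekly at the meetings or mailed".

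**Return, Support Group.** "Subjects may choose to record journal/diary information either electronically (submitted daily) or on paper (submitted weekly at the meetings or mailed".

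**Who is responsible.** In Table 2 the dose-received component is "Participant log of adherence to homework assignments", and the responsible party is the instructors.

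**Masking.** The Masking section says that instructors and subjects cannot be masked. In its paragraph on mailed follow-up questionnaires it adds: "To maintain masking of staff involved in data input and analysis and to prevent bias, returned questionnaires bear only a research number".

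**The concern.** A self-reported outcome in an unmasked trial is already open to expectation. The authors try to limit this: they describe the two interventions neutrally, measure credibility, and have follow-up questionnaires returned under a number only. The paper diary offers a way round that protection. A woman may give the person who taught her that week one sheet with both her practice time and her symptom ratings. She then has a plausible reason to report more practice and fewer symptoms.

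The pull may not be equal in the two arms. Mindfulness leaders assign daily practice, go over it in class and discuss how the program is working. Support leaders are told not to teach, prescribe or advise. What is at stake is the between-arm comparison on the diary and the credibility of the homework minutes as a measure of dose. Because the study is meant to guide the choice of outcomes and to estimate effect sizes for later trials, a collection route adopted here is likely to be carried forward.

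**Working it through.** The article gives no figure to reproduce. The point turns on how an outcome is collected, so the check is to set the sections side by side.

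1. **Is the diary an analysed outcome?** Yes. Table 1 classes it as secondary, and the analytic strategy names GEE for it.
2. **Do symptoms and homework sit on one form?** Yes. The diary description, the Mindfulness homework paragraph and the Quality Control section agree.
3. **Can the form be returned at a meeting?** Yes, in both arms, weekly, if the woman chooses paper and does not mail it.
4. **Does the leader see it?** This is not stated. The article says only that paper is submitted at the meetings. Table 2 makes the instructors responsible for the homework log, and step 2 places that log in the diary. An instructor who carries out that duty with the paper form therefore has the symptom ratings in hand. This is an inference from two stated facts, so the supportable wording is that leaders may see the scores.
5. **Does a stated safeguard cover the diary?** None is stated. The number-only rule appears in the paragraph on mailed follow-up questionnaires.
6. **How much of the diary is exposed?** The programs last 8 weeks and the diary runs 2 weeks beyond them, so it covers 8 + 2 = 10 weeks. At most 8/10 = 80% of diary days fall while weekly meetings are held, and only for women who use paper and hand it in there. The article does not give that share.
7. **Is the primary outcome touched?** No. The IBSS is a separate questionnaire, and its follow-up forms go by mail under a research number.

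To size the bias one would need the share of women returning paper at meetings, by arm, and the shift in reporting that this causes. The article gives neither, so no figure is offered.

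**The case against.** The strongest reply has four parts.

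- **Custody is not described.** Envelopes, labels and who collects the forms are operational details that an article commonly leaves to the full protocol. This stands as a limit: the article does not show that leaders read symptom scores. It does not remove the point, because the article itself fixes the combined form, the return at meetings and the instructors' responsibility for the log.
- **The return options are identical in both arms.** Support members also have homework, and they discuss their symptoms openly before their leader. This stands in part. The procedure creates no difference between arms, and a stronger pull in the Mindfulness arm is plausible but not shown.
- **Subjects are unmasked anyway.** True. Return through the leader could only add to a self-report bias that already exists, by an unknown amount.
- **A change would come late.** The article reports 87 enrolled against a planned 2 × 45 = 90. A new form would then reach few new enrollees and would leave two versions of the diary in the data. This bears on the cost of the fix.

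A reader might also infer that the form tells data-entry staff which arm a woman is in, because practice minutes are mentioned for the Mindfulness diary and a journal for the Support Group. The article does not support that. The diary description gives one instrument with a neutral item on homework minutes, and the Quality Control section speaks of all subjects.

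**Conclusion.** The point holds as a modest design weakness that is cheap to mend. As written, the plan allows unmasked leaders to see the symptom ratings of women who hand in paper diaries at meetings, and it states no safeguard for that route. The likely result is some added reporting bias in one secondary outcome and in dose received, possibly greater in the Mindfulness arm. That rests on two assumptions: that some women use this route, and that the leader's sight of the form affects what they report.

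The size cannot be derived. Web and mailed diaries and the two weeks after the program are less exposed, and the primary IBSS is not affected.

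A reader might go further and conclude that the diary comparison is biased toward Mindfulness by a definite amount. Any such amount would be one assumed number multiplied by another. A reader might also conclude that the third aim, which compares women ranked more and less successful at mindfulness, is distorted. The article does not say that this ranking uses diary minutes, so that consequence is not established.

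**What to change.** - Separate the homework log from the symptom ratings.
- Return the symptom ratings only by web, by mail or in a sealed envelope to the study coordinator, bearing only the research number. Extend the sentence under Masking to cover the diary.
- Tell women in both arms, in the same words, that their leader will not see the ratings.
- Give instructors the homework log alone, which is all that their role in Table 2 requires.

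**Cost.** One form reprinted, some envelopes and a sentence on masking; the web and mail routes already exist. The coordinator handles somewhat more paper. Because women are also asked to record adverse events in the diary, the coordinator must review entries promptly on receipt. Leaders lose sight of the symptom scores. If the change comes late in recruitment, two form versions will exist, so the version and the return route should be recorded for each woman. If it comes too late to be worth making, it should be adopted for the follow-on trial, with the return route reported by arm here where it is known.
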